### Measures

An overview of the measurement points of the primary outcome, secondary outcomes and weekly measures is given in Table 1. All measures, except for the cognitive performance tests and the aerobic fitness test, are self-administered (online questionnaires, sent by email). Completion of the self-administered questionnaires at T0, T6, T7, and T8 will take about 10 min. Participants in the wait list condition will complete the same measures as the participants in the exercise condition (T0-T6), except for the measures of subjective exercise experiences, compliance to the running sessions, and the follow-up measures at 6 and 12 weeks (T7 and T8).

**Table 1 Tab1:** Overview of the measurement points of the primary outcomes, secondary outcomes and weekly measures

	Construct	Pre intervention (T0)	During intervention (every week) (T1-T5)	Post interventionª (T6)	Follow-up after 6 weeks^b^ (T7)	Follow-up after 12 weeks^b^ T8)
Primary outcome	Work-related fatigue:					
	- Emotional exhaustion	√		√	√	√
	- Need for Recovery	√		√	√	√
	- Overall Fatigue	√		√	√	√
Secondary outcomes	Sleep:					
	- Sleep quality	√		√	√	√
	- Sleep quantity	√		√	√	√
	Self-efficacy:					
	- General self-efficacy	√		√	√	√
	- Work self-efficacy	√		√	√	√
	Work ability	√		√	√	√
	Cognitive functioning:					
	- Updating	√		√		
	- Inhibition	√		√		
	- Switching	√		√		
	- Subjective costs of the tests	√		√		
	- Cognitive Failures	√		√		
	Aerobic fitness:					
	- VO_2max_	√		√		
	- Subjective costs of the test	√		√		
Weekly measures	Employee well-being:					
	- Health	√	√√√√√	√		
	- Mood	√	√√√√√	√		
	- Fatigue	√	√√√√√	√		
	- Tension	√	√√√√√	√		
	- Stress	√	√√√√√	√		
	- Energy	√	√√√√√	√		
	- Satisfaction	√	√√√√√	√		
	- Irritation	√	√√√√√	√		
	- Sleep	√	√√√√√	√		
	- Self-efficacy (sport, work, private)	√	√√√√√	√		
	Exercise activities:					
	-Compliance to running sessions^a^		√√√√√	√		
	- (Other) exercise activities	√	√√√√√	√	√	√
	Subjective exercise experiences:					
	- Pleasure^a^		√√√√√	√		
	- Effort^a^		√√√√√	√		
	- Detachment^a^		√√√√√	√		

^a^Compliance to running sessions and subjective exercise experiences will be only collected among participants in the exercise condition, because participants in the control condition receive no running sessions during the intervention period

^b^Follow-up measures will only be collected among participants in the exercise condition, because at the time of the follow-up measures the participants in the control condition receive the exercise intervention

### Primary outcome measures

#### Work-related fatigue

We will use three self-reported indicators to measure work-related fatigue. First, *emotional exhaustion* will be assessed with the subscale ‘Emotional exhaustion’ of the Dutch adaptation of the Maslach Burnout Inventory [58], the Utrecht Burnout Scale (UBOS [59]). The scale consists of 5 items, for example “I feel burned out from my work” (0 = *never*, 6 = *every day*). A mean score equal to or higher than 2.2 on this scale is defined as a ‘high level’ of work-related fatigue [59]. Previous research shows that psychometric properties of this scale are good [60]. Secondly, *overall fatigue* will be measured with the 10-item Fatigue Assessment Scale (FAS [50]). An example question is “I get tired very quickly” (1 = *never*, 5 = *always*). A sum score higher than 21 is indicative of a high level of fatigue [61]. The scale has found to be valid and reliable [50]. Third, *need for recovery* will be assessed by a short version of the ‘Need for Recovery Scale’ [62]. The scale consists of 6 items. An example item is: “Because of my job, at the end of the working day I feel rather exhausted” (1 = *(almost) never*, 4 = *(almost) always*). For this scale, no norm scores are available. Therefore, inclusion was based on the measures UBOS and FAS. Previous research shows that validity is good [62].

### Secondary outcomes measures

#### Self-efficacy

We will use two indicators to measure self-efficacy. First, g*eneral self-efficacy* will be assessed using a Dutch translation of the 12-item General Self-Efficacy Scale [63]. An example item is: “If I made a decision to do something, I will do it” (1 = *strongly disagree*, 5 = *strongly agree*). Psychometric properties of this scale are good [62]. Secondly, w*ork-related self-efficacy* will be measured by means of the subscale ‘Competence’ of the Utrecht Burnout Scale [59]. An example item is: “If I make plans, I am convinced I will succeed in executing them” (0 = *never*, 6 = *every day*). Validity and reliability of the scale are good [60].

#### Sleep

To measure employees’ *sleep quality*, the 6-item sleep quality scale of the Dutch Questionnaire on the Experience and Evaluation of work will be used [64]. The scale measures the three main components of insomnia (i.e. difficulties in: initiating sleep, maintaining sleep, and restorative sleep) and overall sleep. An example item is: ‘I often wake up several times during the night’ (0 = *no,* 1 = *yes*). Furthermore, participants report their average sleep duration (hours, minutes) as an indicator of *sleep quantity*. Reliability and validity of the scale are found to be good [60].

*Work ability* will be measured by means of a single item [65], namely “Can you indicate how you rate your current work ability when you compare it with your life-time best?” (0 = *completely unable to work*, 10 = *work ability at its best*). This item has been shown to be a good alternative to more comprehensive measures of work ability [65].

#### Cognitive functioning

Employees’ cognitive functioning will be measured by means of four indicators: one self-report measure and three cognitive performance tests.

*Self-reported cognitive problems* will be measured with a Dutch translation of the Cognitive Failure Questionnaire (CFQ [66]). This questionnaire measures the frequency of every day cognitive failures and consists of 25 items. An example question is: “Do you read something and find you have not been thinking about it and must read it again?” (1 = *never*, 5 = *very often*). Previous research shows that the CFQ has excellent psychometric properties [67].

Three types of executive functions (i.e. ‘updating’, ‘switching’, and ‘inhibition’), which are considered as basic executive functions and can be clearly and precisely described [68], will be measured with three validated tests. These tests will only be conducted pre (T0) and post (T6) intervention and not at follow up, because of possible learning effects. The tests will be provided in a counterbalanced order to the participants. However, for each participant the order of tests is similar pre and post intervention. Individual appointments in the lab of the university will be planned. Completion of the three cognitive tests, including filling out the subjective costs, takes about 30 min.

*Updating* will be measured with the 2-Back Task [69]*.* Updating refers to the capability of actively manipulating relevant information in working memory [68]. During the task, 284 stimuli (the letters: b, d, g, p, t, and v) are displayed one by one in the centre of the screen. Each letter will be displayed for 450 ms, and the time between the letters will be 750 ms. The letters are presented in a quasi-randomly order in both capital and small letters. When the displayed letter is similar to the letter that is shown two screens before, participants have to push a button on a button-box (target rate: 32.5 %). For a correct response, no distinction is made between capital and small letters. The number of correct responses will be taken as an indicator of updating.

*Switching* refers to the ability to shift between tasks [68], and will be assessed by the Matching Task [70, 71]. In this task, four different geometric figures (a circle, a hexagon, a square, and a triangle), presented in the colors blue, green, red, or yellow are used as stimuli. The task consists of 31 task runs, each consisting of on average six trials (range: 4–8 trials). During a trial, a colored reference figure is displayed in the upper half of the screen, and four colored match figures are shown in the lower half of the screen. Participants will be instructed to match the reference figure to one of the match figures according to shape or color. Whether participants have to match according to shape or color, will be randomly chosen and indicated by a cue that is displayed for 1000 ms. Participants can push one of four buttons on the keyboard which corresponds to one of the four match figures in the lower half of the screen. During one single task run, participants have to match either according to color or shape. The color-shape combinations are shown in a way that there is one ‘right’ option. Half of all task runs consisted of ‘switch’ runs, in which the type of cue differs from the previous run. The other half consists of ‘repetition’ runs, in which the type of cue is identical to the previous run. The duration of the test is approximately six minutes. Both the mean reaction time for switch runs and repetition runs will be used as an outcome measure for switching (for more detailed information about this task, see [70]).

*Inhibition* addresses one’s capability to deliberately inhibit dominant and automatic responses to certain stressors [68]. Inhibition will be measured with the Sustained-Attention-to-Response Test (SART [72]). During this test, digits (ranging from 1–9) are displayed one-by-one in the centre of the screen. Participants are instructed to push a button on a button-box when a digit appears on the screen, except when the digit is a ‘3’, which occurs in 11.1 % of the cases. A total of 450 digits will be presented, each with a duration of 250 ms. The interval between digits is 850 ms. The number of inhibition errors (thus, when a participant presses the button when a ‘3’ appears on the screen), will be taken as a measure for inhibition.

To obtain more insight into cognitive functioning, we will additionally evaluate the *subjective costs* (fatigue, motivation, demands, and effort) associated with doing these tests [73, 74]. These *subjective costs* will be measured using single item measures, answered on a scale from 1 (*not at all*) to 10 (*very much*). Before doing the cognitive tests, participants will rate how motivated they are to do the tests. Fatigue will be measured prior to and after the tests. In addition, after each cognitive test, participants will be asked to score how demanding the test had been. After completing all the tests, participants indicate how much effort they spent when doing the tests.

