### Exercise and cognitive functioning

Fourth, the effect of exercise on cognitive functioning will be studied. Research shows that employees with high levels of work-related fatigue often display cognitive deficits, such as impaired executive functioning and cognitive problems in daily life [36, 37]. Executive functioning refers to a set of cognitive brain processes involving mental control and self-regulation [38]. Evidence from a broad range of studies shows that exercise is linked to beneficial changes in cognitive functioning, in particular executive functions [39, 40]. Therefore, we hypothesize:*Hypothesis 2f:* the exercise intervention is effective in improving cognitive functioning among employees with high levels of work-related fatigue

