### Analyses of primary and secondary outcomes

We will use intention-to-treat analysis, meaning that all participants who are randomized to a condition will be included in the analyses. To test the efficacy of the exercise intervention (i.e. change in primary and secondary outcomes from pre [T0] to post [T6]), we will perform 2x2 repeated measures (M)ANOVAs with condition (exercise versus wait list) as between-subjects factor, and time (pre [T0] versus post [T6]) as within-subjects factor. We will conduct a RM-MANOVA for the three indicators of work-related fatigue together (*Hypothesis 1*). Furthermore, we will conduct separate RM-(M)ANOVAs for respectively self-efficacy (*Hypothesis 2a and 2b*), sleep (*Hypothesis 2c and 2d*), work ability (*Hypothesis 2e*), cognitive functioning (*Hypothesis 2f*), and aerobic fitness (*Hypothesis 2 g*). The Matching Task will be analyzed using a 2x2x2 mixed design ANOVA, with ‘run type’ (switch versus repetition), and time (pre versus post) as within-subjects factors, and condition as between-subjects factor (exercise versus wait list). In all analyses, we are particularly interested in the ‘condition x time’ interaction, because this indicates that the conditions differ from each other with respect to the development of the outcome measure over time. If applicable, significant interactions will be further examined by paired-sample t-tests. Partial eta-squared will be reported as effect size.

Additionally, to obtain more thorough insight into the clinical meaningfulness of the changes brought about by the exercise intervention [81], we will perform a Chi-Square Test to see if the number of participants who score below cut-off scores of fatigue after the intervention period (T6) differs between the intervention and the control condition (emotional exhaustion <2.2 on the UBOS; overall fatigue: <22 on the FAS).

To investigate whether intervention-effects last during the follow-up period, for each primary and secondary outcome measure, a repeated measures MANOVA will be performed to see whether it differs between pre (T0), post (T6), 6 weeks after the intervention period (T7), and 12 weeks after the intervention period (T8). If the overall time effect of MANOVA is significant, post hoc tests will be carried out to exactly determine between what time points the outcome had changed. As follow-up measures are only available for the intervention condition, the control condition will not be included in these analyses.

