### Strengths and limitations

The main strength of this study is its methodological quality: the use of the randomized controlled design, intention-to-treat analysis, follow-up measures, and multi-method measures (self-reports and performance measures). Using these design elements reduces several sources of bias, like selection bias, withdrawal bias, and allows us to make strong causal inferences [85]. As such, the current RCT will add to the existing scientific literature about the effect of exercise on work-related fatigue. Since our intervention will be delivered in a uniform fashion to a specific homogeneous target audience, and thus can be regarded as an ‘efficacy trial’ (i.e., the intervention produces the expected result under ideal circumstances), the results of the current study may also provide a basis for future ‘effectiveness’ trials in which the (implementation of the) intervention can be investigated among a broader defined population in a less standardized way [86].

Another strength is our sample. We choose to investigate employees who are still able to work, but have (relatively) high levels of work-related fatigue. As such, our intervention can be regarded as secondary prevention [87]. We expect that exercise not only reduces work-related fatigue symptoms, but also prevents these from becoming more severe (i.e. clinical burnout [60]). We believe that it is valuable to target these employees, because prevention is better than cure. However, future research could also investigate whether exercise benefits clinical burnout.

Despite its strengths, several issues concerning our study deserve attention. First, our study is not blinded, because active participation of the participants and trainers is necessary in our intervention. Furthermore, because the number and timing of outcome measures differed between the intervention and the control group, it was not possible for researchers involved in this study to be blind to the condition they were assessing. Although blinding is preferable, it should be noted that our primary and secondary outcomes require no subjective evaluation from the outcome assessors. As such, we argue that this issue is of limited influence [88].

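### As naturally read, the test of cognitive functioning (Hypothesis 2f) cannot show whether a significant result comes from self-ratings or from test performance

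*Protocol article*

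**What the plan says.** Hypothesis 2f is a single statement that "the exercise intervention is effective in improving cognitive functioning among employees with high levels of work-related fatigue" (Protocol article, Exercise and cognitive functioning). The Cognitive functioning part of the secondary outcome measures gives four indicators, "one self-report measure and three cognitive performance tests". These are the Cognitive Failure Questionnaire (CFQ), the 2-Back for updating, the Matching Task for switching and the SART for inhibition. On how they are collected, the Measures section says "All measures, except for the cognitive performance tests and the aerobic fitness test, are self-administered", so the CFQ is an online self-rating.

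On the analysis (Analyses of primary and secondary outcomes), the protocol says "we will conduct separate RM-(M)ANOVAs for respectively self-efficacy" and then names the other secondary domains. Cognitive functioning appears as one entry tied to Hypothesis 2f. Only the Matching Task is given a separate model, a 2x2x2 mixed ANOVA. The effect of interest is the condition-by-time interaction. Where applicable, a significant interaction is explored with paired-sample t-tests.

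The Strengths and limitations section states that the trial is unblinded. It also counts the combination of self-report and performance measures as a strength.

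**The concern.** The CFQ and the performance tests differ in how far knowledge of the assigned arm can affect them. The CFQ asks participants, who open their own allocation envelope, how often they have everyday lapses. The 2-Back and SART are scored by counting correct responses and errors, so they are much less open to expectation. The protocol argues that missing blinding matters little because assessors make no subjective judgement. That does not cover the CFQ, where the unblinded participant is the rater.

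If the three scores enter one multivariate test, a significant interaction says only that some combination of them changed differently between arms. Using two kinds of measure is valuable because one can see whether they agree, and an omnibus result does not show this. The risk is a report that exercise improved cognitive functioning when only ratings of daily lapses had moved.

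**Working it through.** **Which indicators share a test.** There are four indicators. The Matching Task has its own ANOVA, which leaves the CFQ, 2-Back and SART for the RM-(M)ANOVA of the domain, so p = 3.

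**What the follow-up can show.** A paired-sample t-test compares T0 with T6 within one arm. It estimates no difference between arms. The protocol itself drops the cognitive tests at follow-up because of possible learning effects. Practice could therefore produce a pre-post gain on the 2-Back or SART in either arm, whether or not exercise does anything. A significant paired t-test on a performance score could then be taken as the source of an interaction that the CFQ produced.

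**How often a CFQ-only change makes the joint test significant.** The protocol gives no power figure for Hypothesis 2f, so there is none to reproduce.

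Inputs:
- From the Sample size section: 108 recruited and about 20% dropout. 108 x 0.8 = 86.4, taken as 86, or n = 43 per arm. Two-sided 5% level.
- Assumed, because the protocol gives no values: a CFQ shift of d = 0.3 to 0.6 SD of the change score, no effect on the 2-Back or SART, and a common correlation r of 0 to 0.5 between change scores.

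For scale, the planning effect of .15 for the primary outcome, taken as f in the within-between interaction, equals d = sqrt(8 x 0.15^2 / (1 - rho)) = sqrt(0.18 / (1 - rho)). This is 0.44 at the printed repeated-measures correlation of .05 and 0.60 at a correlation of .5.

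Formulas: the condition-by-time test of a 2x2 RM-MANOVA is Hotelling's T-squared on change scores.
- Squared distance: D2 = d^2 (1 + r) / [(1 - r)(1 + 2r)]
- Noncentrality: lambda = (n/2) D2
- Reference distribution: F with 3 and 86 - 3 - 1 = 82 df, 5% critical value 2.716

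Example at d = 0.5:
- r = 0: D2 = 0.25, lambda = 21.5 x 0.25 = 5.375, power 45.1%
- r = 0.5: D2 = 0.25 x 1.5 / (0.5 x 2) = 0.375, lambda = 8.06, power 63.5%

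Percentage of trials with a significant result:

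| CFQ shift (SD) | Joint, r = 0 | Joint, r = 0.2 | Joint, r = 0.3 | Joint, r = 0.5 | CFQ tested alone |
|---|---|---|---|---|---|
| 0.3 | 18.0 | 19.0 | 20.4 | 25.5 | 28.0 |
| 0.4 | 29.8 | 31.8 | 34.2 | 43.4 | 45.0 |
| 0.5 | 45.1 | 47.9 | 51.4 | 63.5 | 63.0 |
| 0.6 | 61.5 | 64.8 | 68.7 | 80.7 | 78.5 |

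With 45 per arm (the protocol's 90 before dropout), a 0.5 SD shift gives 47-50% for r of 0 to 0.2, so the exact sample size matters little.

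**Comparison.** The joint test is usually less sensitive to a CFQ-only shift than the CFQ alone. It slightly exceeds it only at r = 0.5 with shifts of 0.5 SD or more. If the performance tests are analysed apart from the CFQ, a CFQ-only shift of any size leaves their test at its nominal 5%.

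**The case against.** **The pooling is inferred.** The M in (M)ANOVA is bracketed, the list includes single-indicator domains, and only Hypothesis 1 is said to have its indicators analysed together. Model membership may be settled in a fuller plan that is not shown. This stands as a limit: the point rests on the natural reading, not on an explicit statement. If the indicators are in fact tested one by one, most of the attribution problem goes. What remains is that the text does not tie the conclusion on Hypothesis 2f to particular indicators.

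**A reader might infer that pooling inflates the chance of a positive result from biased ratings.** The figures do not support that, since testing the CFQ alone would usually be significant more often.

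**A reader might infer that the CFQ should not count towards Hypothesis 2f**, because the Background says "exercise is linked to beneficial changes in cognitive functioning, in particular executive functions". But the same paragraph also motivates the hypothesis with everyday cognitive problems, which the CFQ measures, and the protocol openly names it as an indicator. Removing it would narrow the authors' hypothesis as a matter of preference.

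**A reader might treat any CFQ shift as bias.** It could equally be a real fall in daily lapses. The documents cannot separate the two.

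**Unblinded self-report runs through the whole trial**, including the primary outcome. That is true and disclosed. What is particular here is that self-ratings and performance scores appear to share one test under one label. The paired t-tests, if run per indicator, would give some indication of what moved, but not a comparison between arms.

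**Conclusion.** The point holds as a minor one about interpreting a secondary outcome. On the natural reading of the analysis section, Hypothesis 2f is decided by a joint test that mixes an unblinded self-rating with two performance scores. The only stated follow-up cannot show, between arms, which of them produced a significant result. A questionnaire-only shift of 0.5 SD would make the joint test significant in about 45-64% of trials, and one of 0.3 SD in 18-26%. These figures assume 43 per arm, no effect on the two tests and correlations of 0 to 0.5. The shifts and correlations are assumptions, and the upper ends depend on a correlation of 0.5. The harm is misattribution, not a raised error rate.

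**What to change.** In Analyses of primary and secondary outcomes:

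1. Analyse self-reported cognitive problems (CFQ) separately from the performance tests.
2. Give a between-arm (condition-by-time) estimate with 95% CI for the CFQ and for each performance test, in place of relying on paired t-tests.
3. Word the conclusion on Hypothesis 2f by source: self-reported, performance, or both.

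The CFQ may stay as an indicator of Hypothesis 2f. No new data are needed. The cost is a change of wording and several results for this domain instead of one.

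### The 2-Back is scored by the number of correct responses; read as hits, the score rises with more liberal button-pressing even when discrimination does not improve

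*Protocol article*

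**What the plan says.** The protocol article describes the 2-Back under Secondary outcomes measures, Cognitive functioning. On the stimuli it says: "During the task, 284 stimuli (the letters: b, d, g, p, t, and v) are displayed one by one in the centre of the screen". The proportion of targets is given as "target rate: 32.5" %. The required action is: "When the displayed letter is similar to the letter that is shown two screens before, participants have to push a button on a button-box". No action is described for non-targets. The score is then fixed in one sentence: "The number of correct responses will be taken as an indicator of updating". The text mentions no false alarms, sensitivity index or other correction for this task, and the section Analyses of primary and secondary outcomes adds none.

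For the inhibition test (SART) the same section does count wrong presses: "The number of inhibition errors (thus, when a participant presses the button when a ‘3’ appears on the screen), will be taken as a measure" of inhibition.

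The updating score serves Hypothesis 2f, that "the exercise intervention is effective in improving cognitive functioning among employees with high levels of work-related fatigue". It is measured at T0 and T6 and analysed by repeated measures (M)ANOVA, with the condition x time interaction as the effect of interest.

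**The concern.** The protocol says of the construct: "Updating refers to the capability of actively manipulating relevant information in working memory". A score for it should rise when the participant distinguishes targets from non-targets better. A count of hits also rises when the participant simply presses more readily. Doubtful letters then get a press, more targets are caught, and the extra presses on non-targets cost nothing.

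The interpretation of Hypothesis 2f is at stake. If one arm became more willing to press between T0 and T6 and the other did not, a hit count would show better updating in that arm, and the stated score alone could not tell this from a real gain. Participants know their arm. The article's defence of the unblinded design (Strengths and limitations) is that outcomes need no subjective evaluation by assessors, and that does not address how participants choose to respond.

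**Working it through.** The protocol gives no figure to reproduce here, because the point concerns a scoring rule.

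**Inputs from the protocol article (Cognitive functioning).** 284 letters; target rate 32.5%.
- Targets: 0.325 x 284 = 92.3, taken as 92.
- Non-targets: 284 - 92 = 192.

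**Inputs not in the protocol (assumptions).** Hit and false-alarm rates, sensitivity d' and response criterion c. They are used only to show direction and order of size.

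**Step 1: limiting case.** Pressing on every letter gives 92 hits of 92, the maximum, with 192 false alarms and d' = 0.

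**Step 2: illustration with assumed rates.** d' = z(hit rate) - z(false-alarm rate).

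| | Before | After |
|---|---|---|
| Hit rate, false-alarm rate | 80%, 5% | 90%, 20% |
| Hits | 0.80 x 92 = 73.6 | 0.90 x 92 = 82.8 |
| False alarms | 0.05 x 192 = 9.6 | 0.20 x 192 = 38.4 |
| d' | 0.842 + 1.645 = 2.49 | 1.282 + 0.842 = 2.12 |
| Hit rate minus false-alarm rate | 0.75 | 0.70 |
| Hits + correct rejections | 73.6 + 182.4 = 256.0 | 82.8 + 153.6 = 236.4 |

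The hit count improves by about 9. Both measures that use false alarms get worse.

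**Step 3: range of assumptions.** In the equal-variance signal detection model, hit rate = Phi(d'/2 - c) and false-alarm rate = Phi(-d'/2 - c). A lower c means more liberal pressing.

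| d' | c | Hits (of 92) | False alarms (of 192) | Hits + correct rejections (of 284) |
|---|---|---|---|---|
| 2.0 | +0.5 | 63.6 | 12.8 | 242.8 |
| 2.0 | 0 | 77.4 | 30.5 | 238.9 |
| 2.0 | -0.5 | 85.9 | 59.2 | 218.6 |
| 2.5 | +0.5 | 71.2 | 7.7 | 255.5 |
| 1.5 | -0.5 | 82.3 | 77.0 | 197.2 |
| 1.0 | -0.5 | 77.4 | 96.0 | 173.4 |

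- At fixed d' = 2.0, looser pressing alone lifts hits from 63.6 to 85.9.
- Going from d' = 2.5, c = +0.5 to d' = 1.5, c = -0.5, hits rise from 71.2 to 82.3 although discrimination is clearly worse.
- A participant with d' = 1.0 and c = -0.5 gets the same 77.4 hits as one with d' = 2.0 and c = 0.

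The direction does not depend on the values chosen. At fixed d', lowering c can only raise the hit rate.

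**Step 4: the other reading.** If correctly withheld presses also count, false alarms reduce the score, and the last column shows liberal pressing being penalised. Style still matters: at the same d' = 2.0 the total runs from 242.8 down to 218.6. With no discrimination at all, never pressing scores 192/284 = 68% and always pressing scores 92/284 = 32%. The two readings can therefore move in opposite directions on the same data.

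**The case against.** The strongest objection is that the article does not define a correct response and nowhere says that false alarms are excluded. On the total-accuracy reading the score falls when discrimination falls in the illustration, and never pressing (68%) does worse than ordinary performance (256/284 = 90%). This stands as a limit: the claim that liberal pressing is rewarded holds only on the hits reading. That reading is still the natural one, because the only response described is a press on a target. It might also be said that scoring detail belongs in a fuller document. Here, however, the article does not leave the score open; it states a rule, and the rule can be assessed.

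A second objection is that participants are compared with themselves and the test is condition x time. A stable pressing style, or a shift common to both arms, largely cancels. The protocol also records motivation, fatigue, demand and effort around the tests at T0 and T6, so an arm difference in motivation would be visible. Both observations stand. The ratings do not correct the score, but they weaken the case that a shift would go unnoticed.

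Three stronger conclusions might be inferred, and the documents do not support them:
- **That the Hypothesis 2f comparison is biased.** This needs a shift in style that differs between arms. Lack of blinding makes that possible, but nothing in the article shows it, and higher motivation could equally improve discrimination.
- **That the score rewards liberal pressing on any reading.** It does not if correct rejections count.
- **That the SART has the same fault in reverse.** Presses on the digit 3 match the protocol's own description of inhibition as withholding a dominant response. Adding omissions and go-trial reaction time would be optional extra reporting.

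**Conclusion.** The concern holds for the 2-Back, at minor importance. On the natural reading the updating score is a hit count that cannot separate better discrimination from readier pressing, and it can rise while discrimination falls (74 to 83 hits with d' from 2.49 to 2.12, under assumed rates). On the alternative reading that direction reverses (256 to about 236 of 284), though some dependence on style remains. The term therefore needs defining in either case.

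The conclusion rests on taking a correct response to mean a press on a target. The sizes rest on illustrative rates that are not in the protocol; the direction does not. Distortion of the condition x time test is a possibility only. The 2-Back is one of four cognitive indicators within one of five secondary outcomes, and the primary outcome and sample size are unaffected.

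**What to change.** In the 2-Back paragraph, replace the scoring sentence with one stating that updating is scored as d', with a standard correction when a hit or false-alarm rate is 0% or 100%, or as hit rate minus false-alarm rate. Use that score in the planned condition x time analysis for Hypothesis 2f.

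Of the two, d' is free of the criterion under the equal-variance model. The simple difference is nearly so: from the model above at d' = 2.0, it is 0.691 - 0.067 = 0.624 at c = +0.5, 0.841 - 0.159 = 0.682 at c = 0, and 0.933 - 0.309 = 0.624 at c = -0.5. The difference in rates needs no correction at the extremes.

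The cost is a change in scoring and one sentence of text. It adds no data collection or participant burden, provided the button-box record keeps presses on non-targets as well as on targets.
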